### 2.4.3.2 Trials of VEGFR and EGFR combination therapy in glioblastoma

| Trial title                                                                                                                                                                            | Phase | Identifier  | Recruiting |
|----------------------------------------------------------------------------------------------------------------------------------------------------------------------------------------|-------|-------------|------------|
| Phase II Bevacizumab + Erlotinib for Patients With Recurrent Malignant Glioma                                                                                                          | II    | NCT00671970 | No         |
| Combination of Bevacizumab, Pertuzumab, and Sandostatin for Advanced Neuroendocrine Cancers                                                                                            | II    | NCT01121939 | Yes        |
| Bevacizumab and Lapatinib in Children With Recurrent or Refractory Ependymoma                                                                                                          | II    | NCT00883688 | Yes        |
| Zactima With Temodar During Radiation Treatment for Newly Diagnosed Stage IV Brain Tumors                                                                                              | I/II  | NCT00441142 | Yes        |
| Ph I Dose Escalation Trial of Vandetanib in Combo w Etoposide for Malignant Gliomas                                                                                                    | I     | NCT00613223 | Yes        |
| Investigate the Maximum Tolerated Dose of Vandetanib and Concurrent Whole Brain Radiotherapy (WBRT) in Patients With Non-small Cell Lung Cancer (NSCLC) and Brain Metastases           | I     | NCT00807170 | Yes        |
| Ph I Zactima + Imatinib Mesylate & Hydroxyurea for Pts w Recurrent MG                                                                                                                  | II    | NCT00613054 | Yes        |
| A Randomized Phase II Trial of Vandetanib (ZD6474) in Combination With Carboplatin Versus Carboplatin Alone Followed by Vandetanib Alone in Adults With Recurrent High-Grade Gliomas   | II    | NCT00995007 | Yes        |
| Vandetanib and Radiation Therapy in Treating Young Patients With Newly Diagnosed Diffuse Brainstem Glioma                                                                              | I     | NCT00472017 | No         |
| ZD6474 Alone and in Combination With Retinoic Acid in Pediatric Neuroblastoma                                                                                                          | I     | NCT00533169 | Yes        |
| Phase I Dose Escalation Study of Vandetanib w/ Hypofractionated Stereotactic Radiotherapy in Patients w/ Recurrent Malignant Gliomas                                                   | I     | NCT00822887 | Yes        |
| Vandetanib and Sirolimus in Patients With Recurrent Glioblastoma                                                                                                                       | I     | NCT00821080 | Yes        |
| Clinical Trial Evaluating the Combination of Vandetanib and Dasatinib During and After Radiation Therapy (RT) in Children With Newly Diagnosed Diffuse Intrinsic Pontine Glioma (DIPG) | I     | NCT00996723 | Yes        |
| ZD6474 in Treating Patients With Recurrent or Progressive Gliomas                                                                                                                      | I/II  | NCT00293566 | No         |

**Table 4** *Trials of combination anti-VEGF and EGFR therapy in brain cancer*  
([www.clinicaltrials.gov](http://www.clinicaltrials.gov))

Early studies using single agent targeted therapies directed against EGFR in patients with recurrent glioblastoma have shown disappointing results (Franceschi et al. 2007; Rich et al. 2004). As mentioned above, such resistance to anti-EGFR therapy is thought to result, in part, from

upregulation of VEGF and other pro-angiogenic molecules by tumour cells, imparting upon them a higher angiogenic potential (Ciardiello et al. 2004; Naumov et al. 2009; Vitoria-Petit et al. 2001; Vitoria-Petit and Kerbel 2004). This has clear implications for the single agent use of EGFR targeted therapy in the 'avidly vascular' model of glioblastoma, and is the basis of the move to develop clinical trials examining the efficacy and safety of anti-VEGF and anti-EGFR targeted therapy in combination in recurrent glioblastoma. The combined EGFR/VEGF blocking agent AEE788 was well tolerated in a Phase I study in patients with recurrent glioblastoma. Seven (27%) patients achieved stable disease and progression free survival at 6 months was 14% (Reardon et al. 2005). Another combined EGFR/VEGF blocking agent vandetanib has been studied in a phase I study in combination with etoposide in recurrent glioblastoma patients. At dose level 1, higher than expected rates of grade 4 neutropaenia were observed. Consequently the dose level has been reduced, and dose escalation continues. A phase II trial is planned when the maximum tolerated dose of vandetanib with reduced dose etoposide is determined (Herndon et al 2009). In a recent phase II trial Hasselbalch et al treated forty-three patients with recurrent glioblastoma with a combination of cetuximab, bevacizumab and irinotecan. Radiological responses were noted in 34% of patients, of which two had complete responses and nine had partial responses. The 6-month progression-free survival probability was 30% and median overall survival was 29 weeks (95% CI: 23–37 weeks). However this was non-superior compared with results with bevacizumab and irinotecan alone (Hasselbalch et al. 2010). In a phase II trial of bevacizumab plus erlotinib in twenty-five patients with recurrent glioblastoma, twelve patients (48%) achieved radiological response and 6 month progression-free survival rate was 24% (Sathornsumetee et al 2008). The combination was well tolerated, with common side effects being rash, diarrhoea, mucositis and fatigue.

Given that the recent phase I study combining cediranib with gefitinib demonstrated combination treatment to be generally well tolerated, and to show encouraging antitumour activity in patients with advanced solid tumours (van Cruijsen et al. 2010), we aim to follow on directly from this and both build on the experience with cediranib as a single agent in recurrent/progressive glioblastoma and investigate whether the efficacy of cediranib is improved with the addition of gefitinib.

## 2.5 Proposed Trial

This is a phase II, randomised, double blind placebo controlled study in patients with recurrent or progressive glioblastoma (WHO grade IV). Patients are to receive cediranib in combination with gefitinib or cediranib with placebo.

### 2.5.1 Primary Objective

- The primary objective of the study is to compare the efficacy of cediranib in combination with oral gefitinib with cediranib alone.

### 2.5.2 Secondary Objectives

- To document the safety and tolerability of cediranib in combination with oral gefitinib and cediranib alone.
- To compare cediranib in combination with oral gefitinib and cediranib alone in terms of steroid sparing effects
- To document the quality of life and neurological symptoms reported by patients taking cediranib in combination with oral gefitinib and cediranib alone.
- To investigate the relationship between the effects of cediranib (+/- gefitinib) on levels of soluble angiogenesis biomarkers and clinical efficacy
- To investigate the relationship between the patient's genetic profile and efficacy of cediranib (+/- gefitinib)

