### 2.6.2 Patient reported outcomes (PROs)

- Neurological symptoms (visual disorder, motor dysfunction, communication deficit, and drowsiness) as measured by the EORTC brain tumour module BN-20.
- Quality of life as measured by the EORTC QLQ-C30 and other domains as measured by BN-20 questionnaire

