The number of progression/steroid free days is the number of days that a patient is known not to have used any steroids (dexamethasone) prior to progression. This will be summarized by treatment group.

- **Time to deterioration of neurological status or death**

This endpoint will be summarized by treatment group. Neurological status based on investigator's neurological examination prior to and during treatment will be recorded on the CRF.

Patient's last pre-dose assessment will be defined as baseline. Patients without a baseline assessment will be excluded from analysis. Time to neurological status deterioration will be defined as the date of randomization to the date of first neurological status worsening in comparison to baseline (first of 2 confirmatory reports at 2 consecutive visits, 6 weeks apart) as assessed by the clinician, or until date of death, whichever is first.

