### Quality of Life

- **EORTC QLQ-C30**

Each domain will be summarised. The change from baseline will be summarized. For specific domains, a model based analysis will be undertaken (such as Mixed effects models). The scoring of the items/scales will be as described in the EORTC QOL Scoring Manual. Patients without a baseline assessment will be excluded from the analysis.

- **EORTC brain tumour module BN-20 questionnaire - Neurological symptoms (visual disorder, motor dysfunction, communication deficit, and drowsiness)**

Patients with recurrent glioblastoma commonly experience neurological symptoms. Therefore, improvement in visual disorders, motor dysfunction, communication deficits and drowsiness between the treatment arms for patients with neurological symptoms relative to baseline will be summarized by treatment group. Improvement in symptoms should also be concurrent with stable or decreasing use of steroids (dexamethasone). Visual disturbances will be assessed using questions 36, 37 and 38 of the BN-20. Motor dysfunction will be assessed using questions 40, 45, and 49 of the BN-20.

Communication deficits will be assessed using question 41, 42 and 43 of the BN-20. Drowsiness will be assessed by question 44.

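### Section 16.4 states the BN-20 neurological-symptom analysis as improvement among symptomatic patients, so new or worsening patient-reported symptoms are not summarised by arm, although the objective sets no such limit (minor)

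*Protocol*

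**What the plan says.** Section 2.5.2 gives the objective as "To document the quality of life and neurological symptoms reported by patients taking cediranib in combination with oral gefitinib and cediranib alone".

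Section 2.6.2 lists two patient-reported outcomes. The first is four neurological symptom groups (vision, motor function, communication, drowsiness) "as measured by the EORTC brain tumour module BN-20". The second is "Quality of life as measured by the EORTC QLQ-C30 and other domains as measured by BN-20 questionnaire". Neither entry names a direction of change or a subset of patients.

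Section 16.4, under Quality of Life, gives the analysis:

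- For QLQ-C30: "Each domain will be summarised. The change from baseline will be summarized". Patients with no baseline assessment are left out, and models are foreseen for some domains.
- For BN-20, what is to be summarised by arm is "improvement in visual disorders, motor dysfunction, communication deficits and drowsiness between the treatment arms for patients with neurological symptoms relative to baseline". The improvement should coincide with a dexamethasone dose that is stable or falling. The items that make up each of the four symptom groups are then listed.

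No other BN-20 analysis is stated.

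**The concern.** The objective asks what patients report on each regimen. The stated BN-20 summary answers a narrower question: how many symptomatic patients got better without more steroid. A patient free of a symptom at entry cannot improve on it and so adds nothing to the summary, even if the symptom develops during treatment. A patient whose existing symptom gets worse appears only as not improved, together with those who stayed the same.

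What is at stake is the descriptive account of patient-reported symptoms when gefitinib is added to cediranib. Two arms with the same improvement rate could differ in new or worsening symptoms, and this display would not show it. An arm with somewhat more improvement and also more worsening would look the better of the two.

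**Working it through.** The protocol gives no BN-20 figure to reproduce, so the check is mainly of the text.

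**Direction and subset**

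| Place | Direction | Patients |
|---|---|---|
| 2.5.2, objective | not limited | all, both arms |
| 2.6.2, outcomes | not limited | not limited |
| 16.4, QLQ-C30 | change from baseline, either way | all with a baseline form |
| 16.4, BN-20 | improvement, dexamethasone not rising | those with neurological symptoms |

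The narrowing happens only in the last row. The row above it, in the same section, shows the broader form written out for the other questionnaire.

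**Items covered.** BN-20 runs from item 31 to item 50 (Appendix 6), which is 20 items. Section 16.4 uses items 36, 37, 38 (vision), 40, 45, 49 (motor), 41, 42, 43 (communication) and 44 (drowsiness): 3 + 3 + 3 + 1 = 10. The other 10, including headaches, seizures and itching, belong to the further BN-20 domains in 2.6.2 and have no analysis stated in 16.4.

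**Where worsening is captured**

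- The section 16.4 endpoint that times neurological decline or death: "Neurological status based on investigator's neurological examination prior to and during treatment will be recorded on the CRF". This is the clinician's assessment.
- Clinical progression in section 2.6.1.1: decline in performance status, judged by site staff.
- Adverse events and neurological examination in section 16.5.

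All of these see worsening. None uses the BN-20 answers.

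**Can an improvement summary rank the arms the other way from net change?** The protocol gives no baseline symptom rate and no rates of change, so every rate here is an assumption chosen to test whether reversal is possible. There are 56 patients per arm (112 randomised 1:1; section 16.5 also uses 56). Let s be the share symptomatic, i the improved and w the worsened among them, and n the newly symptomatic among the rest.

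- The planned summary reports i.
- Worse or new, in all patients = s·w + (1 − s)·n.
- Net change = s·i − s·w − (1 − s)·n.

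Assume arm A has i = 40%, w = 50%, n = 40%, and arm B has i = 30%, w = 20%, n = 15%. At s = 50% there are 28 symptomatic patients per arm:

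- Improved: A 28 × 0.40 = 11.2; B 28 × 0.30 = 8.4.
- Worse or new: A 28 × 0.50 + 28 × 0.40 = 25.2 (45%); B 28 × 0.20 + 28 × 0.15 = 9.8 (17.5%).
- Net: A (11.2 − 25.2)/56 = −25%; B (8.4 − 9.8)/56 = −2.5%.

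| s | Outside the summary, per arm | Reported improvement, A v B | Worse or new, A v B | Net, A v B |
|---|---|---|---|---|
| 30% | 39 | 40% v 30% | 43% v 16.5% | −31% v −7.5% |
| 50% | 28 | 40% v 30% | 45% v 17.5% | −25% v −2.5% |
| 70% | 17 | 40% v 30% | 47% v 18.5% | −19% v +2.5% |

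Under these rates A is reported ahead and is behind on net change at each value of s. If w and n were equal in the two arms, the net difference would be s × (40% − 30%), in favour of A, and there would be no reversal. The exercise shows that reversal can happen, not that it is likely.

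**The case against.** The strongest reply is that the trial does look for worsening. Investigator-assessed neurological decline is a secondary endpoint summarised by arm, clinical deterioration counts as progression in the primary endpoint, and adverse events are tabulated. This stands. A reader might infer that deterioration is never compared, or that harm from gefitinib would go unseen; the documents do not support that. The gap is confined to patient-reported BN-20.

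A reader might also cite the median of 126 days to neurological deterioration on cediranib alone (section 2.4.1.1) as proof that an improvement summary misses most of the change. It is not proof: that figure is for a neurological-status endpoint, not BN-20.

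The objective says *document*, whereas the steroid objective says *compare*, so no test is owed. This is also right, and the fix asks only for summaries. But documenting symptoms includes those that appear or worsen.

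Section 16.4 does not say that nothing else will be tabulated, and an SAP could add tables. This stands in part. The missing tables for the other BN-20 domains are largely SAP detail and would not be a finding alone. For the four symptom groups, however, the protocol does state an analysis, and that analysis is one-sided; an SAP that follows it inherits the gap.

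Finally, the text does not literally say symptomatic at baseline. That is so, but only a patient with a symptom at entry can improve on it, so the reading is fair. Whether one qualifying symptom of the four is enough is not stated, which is a further reason why the number left out cannot be fixed.

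**Conclusion.** The point holds as a minor one. Sections 2.5.2 and 2.6.2 set out to record patient-reported neurological symptoms in each arm without limit, while section 16.4 states the BN-20 analysis in one direction and in a subset. Followed as written, new and worsening patient-reported symptoms are not summarised by arm, and the display could favour an arm with more of both improvement and worsening.

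The size is unknown. It depends on the share of patients symptomatic at entry and on the rates of change in each arm, none of which the protocol gives. A reader might take the illustration as a forecast that the arms will be ranked wrongly; it rests on assumed rates and shows only that this can occur. The outcome is descriptive and secondary, and the PFS conclusion and the sample size do not depend on it.

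**What to change.** In section 16.4, state that BN-20 change from baseline will be summarised by arm for all patients with a baseline form, in line with what is already written for QLQ-C30. Give the proportions improved, unchanged and worsened, counting patients who become newly symptomatic as worsened. Do this for the four symptom groups and for the other BN-20 domains named in 2.6.2. Keep improvement on stable or decreasing dexamethasone as an additional display. The cut-offs that define improved and worsened can be left to the SAP.

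The cost is some analysis wording and a few more descriptive tables. No new data are needed: section 8.1 already schedules BN-20 at baseline, week 6, every 12 weeks from week 18, and discontinuation.

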## 2.6 Outcome variables

### 2.6.1 Efficacy

#### 2.6.1.1 Primary outcome variable

Progression free survival (PFS) defined as the time from the date of randomisation to the date of first progression or death due to any cause, whichever one comes first.

The progression definition will be based on modified RANO criteria (Wen 2010), such that progression will be defined as the earliest time that at least one of the following occurs:

*As assessed by site staff at clinical assessments:*

1. **Clinical deterioration** not attributable to other causes apart from the tumour (e.g seizures, medication adverse events, complications of therapy, cerebrovascular events, infection, and so on) or changes in dexamethasone dose.

Clinical deterioration will be defined as:

- Decline in Karnofsky performance status from 100 or 90 to 70 or less, or a decline of at least 20 from 80 or less, or a decline from any baseline to 50 or less, for at least 7 days

- Decline in ECOG performance status from 0 or 1 to 2 or 2 to 3

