#### 7.4.1.8 Fatigue

Fatigue experienced by patients taking cediranib and/or gefitinib may be rapid in onset. During appointments patients should be specifically interrogated about fatigue, and estimated fatigue levels (according to CTC) should be recorded.

Patients should seek medical advice early if Grade 2 fatigue develops (moderate fatigue causing difficulty performing some activities of daily living).

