## 8.2 Schedule of Assessments – further details

### a) Physical Examination

Including height, weight, lying and 5 minute standing blood pressure, ECOG performance status. Patient's blood pressure needs to be monitored weekly for the first 6 weeks of treatment of cediranib +/- gefitinib. Patients/carers will monitor the patient's blood pressure daily and record this in the patient diaries. CRFs should reflect an average of the patient-reported daily values. If a patient has BP  $\geq 150/100$  mmHg at Screening, a further reading should be taken at least 24 hours later to assess eligibility. In event of hypertension, refer to hypertension management plan, see [Section 7.4.1.4](#).

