## Appendix 5: Performance Status Evaluation

### ECOG PERFORMANCE STATUS

| Grade | ECOG                                                                                                                                                      |
|-------|-----------------------------------------------------------------------------------------------------------------------------------------------------------|
| 0     | Fully active, able to carry on all pre-disease performance without restriction                                                                            |
| 1     | Restricted in physically strenuous activity but ambulatory and able to carry out work of a light or sedentary nature, e.g., light house work, office work |
| 2     | Ambulatory and capable of all selfcare but unable to carry out any work activities. Up and about more than 50% of waking hours                            |
| 3     | Capable of only limited selfcare, confined to bed or chair more than 50% of waking hours                                                                  |
| 4     | Completely disabled. Cannot carry on any selfcare. Totally confined to bed or chair                                                                       |
| 5     | Dead                                                                                                                                                      |

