### KARNOFSKY PERFORMANCE STATUS SCALE DEFINITIONS RATING (%) CRITERIA

|                                                                                                                     |     |                                                                                     |
|---------------------------------------------------------------------------------------------------------------------|-----|-------------------------------------------------------------------------------------|
| Able to carry on normal activity and to work; no special care needed.                                               | 100 | Normal no complaints; no evidence of disease.                                       |
|                                                                                                                     | 90  | Able to carry on normal activity; minor signs or symptoms of disease.               |
|                                                                                                                     | 80  | Normal activity with effort; some signs or symptoms of disease.                     |
| Unable to work; able to live at home and care for most personal needs; varying amount of assistance needed.         | 70  | Cares for self; unable to carry on normal activity or to do active work.            |
|                                                                                                                     | 60  | Requires occasional assistance, but is able to care for most of his personal needs. |
|                                                                                                                     | 50  | Requires considerable assistance and frequent medical care.                         |
| Unable to care for self; requires equivalent of institutional or hospital care; disease may be progressing rapidly. | 40  | Disabled; requires special care and assistance.                                     |
|                                                                                                                     | 30  | Severely disabled; hospital admission is indicated although death not imminent.     |
|                                                                                                                     | 20  | Very sick; hospital admission necessary; active supportive treatment necessary.     |

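### The ECOG route to clinical progression has no minimum duration, so a brief fall not recognised as toxicity can bypass the 7-day rule on the Karnofsky route

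*Protocol*

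**What the plan says.** Section 2.6.1.1 makes progression the earliest time at which any one of six criteria is met. The first, clinical deterioration, is assessed by site staff. Its lead-in admits only decline that is not explained by something other than the tumour, and it names drug adverse events, treatment complications and dexamethasone changes among the excluded explanations. Two bullets then define the decline:

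- The Karnofsky bullet has three limbs. Two depend on the size of the fall, and the third is met when the score reaches 50 or lower, whatever its starting value. The bullet ends with a minimum duration of 7 days.
- The ECOG bullet reads in full: "Decline in ECOG performance status from 0 or 1 to 2 or 2 to 3".

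The duration stands only in the Karnofsky bullet. I read it as governing all three Karnofsky limbs; on any reading it does not reach the ECOG bullet. A clinical event is dated when it was first reported.

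ECOG is part of the physical examination (section 8.2 a: "Including height, weight, lying and 5 minute standing blood pressure, ECOG performance status"). The schedule in section 8.1 places that examination at every week from 1 to 6, then at the 6-weekly cycle starts and at discontinuation. In weeks 1 to 6 Karnofsky is scheduled at weeks 3 and 6 only.

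**The concern.** The 7-day condition protects the primary endpoint against short-lived falls. Because either bullet suffices, a single ECOG reading can produce an event without that protection, and in the first cycle ECOG is the scale read more often.

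This is also the period in which attribution is difficult. Section 7.4.1.8 warns: "Fatigue experienced by patients taking cediranib and/or gefitinib may be rapid in onset". The protocol expects such problems to be managed with short breaks: 2 to 3 days for fatigue (7.4.1.8) and 2 to 5 days for multiple low-grade events (7.4.1 and 7.4.2). A fall of that length is what a 7-day rule would filter out, provided the site had not already identified it as toxicity.

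Elsewhere the protocol asks for confirmation. In section 16.4, neurological deterioration needs two consecutive visits 6 weeks apart, and complete or partial response needs two consecutive scans. A wrongly called clinical event may also be hard to correct, because a patient who discontinues for progression moves to 12-weekly telephone follow-up for survival (section 8.2 h). Events unrelated to the tumour dilute the treatment effect even when they are equally common in both arms.

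**Working it through.** **The two routes side by side**

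| | Karnofsky | ECOG |
|---|---|---|
| Duration | at least 7 days | none stated |
| Scheduled readings, weeks 1 to 6 | 2 (weeks 3, 6) | 6 (weekly) |
| Attribution lead-in applies | yes | yes |
| Central review | no | no |

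**Size of fall.** Appendix 5 describes Karnofsky 70 as "Cares for self; unable to carry on normal activity or to do active work" and ECOG 2 as "Ambulatory and capable of all selfcare but unable to carry out any work activities". These describe nearly the same state. From a Karnofsky baseline of 80, a fall to 70 is 10 points. The Karnofsky line asks for "a decline of at least 20 from 80 or less", so it rejects this fall, while a matching move from ECOG 1 to 2 meets the ECOG line. Such patients are expected: entry requires Karnofsky 70 or above (5.1.1), and 80 or below is a stratification level (6.1). The mapping is inferred from the wording, since the protocol gives no crosswalk.

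The mismatch in size is narrow. Karnofsky 90 to 70 meets the Karnofsky line, 60 to 50 meets its third limb, and ECOG 0 to 1 does not count. The mismatch in duration covers the whole ECOG bullet.

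**The plan's own figure (section 16.1).** Inputs: medians of 4 and 6 months, hazard ratio 4/6 = 0.6667, one-sided 10%, power 80%, 1:1 allocation.

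- Events = 4 × (1.2816 + 0.8416)² / (ln 0.6667)² = 4 × 4.508 / 0.1644 = 109.7, so 110. This matches the stated 110.
- Power at 110 events = Φ(√110/2 × 0.4055 − 1.2816) = Φ(0.845) = 80.1%.

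**Illustration, with an assumed rate.** The protocol gives no rate of misattributed falls. Let f be the share of control-arm events that are such falls, and let the same hazard s be added in both arms. Hold 110 events.

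- λ_control = ln 2 / 4 = 0.1733; λ_combination = ln 2 / 6 = 0.1155
- s = 0.1733 × f / (1 − f)
- HR = (0.1155 + s) / (0.1733 + s)
- Power = Φ(√110/2 × |ln HR| − 1.2816)

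| f (assumed) | s | HR | Power |
|---|---|---|---|
| 0 | 0 | 0.667 | 80.1% |
| 5% | 0.0091 | 0.683 | 76.3% |
| 10% | 0.0193 | 0.700 | 72.2% |
| 20% | 0.0433 | 0.733 | 63.5% |

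**The case against.** The strongest answer is the lead-in to the two bullets. It excludes deterioration due to drug adverse events or treatment complications, so a reader who infers that transient toxicity becomes a PFS event goes further than the text allows. That stands: recognised toxicity, brief or not, is not an event. What remains is misattribution. The lead-in governs the Karnofsky bullet equally, yet that bullet still carries a 7-day condition, so the protocol does not treat attribution alone as sufficient there.

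A reader might also infer a bias against the combination, because gefitinib is given in one arm only. The protocol does not support this. The fatigue warning covers both drugs, and cediranib is given in both arms. Site staff are blinded, and causality is judged as if the patient were on active treatment (10.2.1.4). More visible gefitinib toxicity could even make correct exclusion more likely.

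It is also fair to say that alternative criteria are meant to differ, so disagreement between the two lines is not in itself a contradiction. The point is narrower: one line carries a safeguard that the other lets the same decline avoid. The exploratory analysis on unmodified RANO criteria (16.3) does not change the definition used for the primary analysis.

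**Conclusion.** The point holds as an inconsistency in the definition of the primary endpoint. A brief ECOG fall that the site does not recognise as toxicity counts as progression without the persistence required on the Karnofsky route. On the Appendix 5 wording this includes a decline resembling Karnofsky 80 to 70.

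The size is unknown. The power range in the table depends wholly on assumed shares of 5% to 20%, a constant and equal added hazard in both arms, and 110 events. It shows what equal misclassification would cost, and does not predict how often it will occur. No difference between arms is shown. The sample size calculation reproduces and is not affected. This should be corrected, but it does not undermine the design.

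**What to change.** In section 2.6.1.1, apply the same minimum of 7 days to the ECOG bullet and date the event to the first reading. State that persistence may be established by the same means as for Karnofsky: a reassessment or documented history at 7 days or more. Declines followed by death or failure to return stay under item 2 of the definition.

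Two tempting additions should be left out. Confirmation at the next scheduled visit would not work: after week 6 ECOG is read only every 6 weeks and at discontinuation, and none is scheduled in long-term follow-up. A carve-out for falls equivalent to Karnofsky 80 to 70 would need a crosswalk that the protocol does not contain.

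The cost is about one sentence, and confirmed declines keep their original date. A few true declines first seen at the discontinuation visit may need a follow-up contact to document persistence. Sections 7.1 and 7.2 refer to 2.6.1.1 for treatment continuation, so the amendment should say whether the new wording concerns only the counting and dating of the endpoint; its bearing on treatment is for the clinical team.
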